**6.4.1. Analysis for Specific Aim 4**

Multivariable logistic regression will be used to ascertain whether 3-month finasteride PSA velocity adds independent diagnostic information for predicting cancer outcome on biopsy relative to the PCPT risk factors: PSA, DRE, family history and prior biopsy on this N=360 cohort. 3-month finasteride PSA velocity will be declared to add independent diagnostic information to the risk factors if it retains statistical significance at the 0.05 level when included in the multivariable logistic regression along with all other risk factors. This particular analysis may have limited power since the cohort is relatively small and several risk factors will be estimated.

An analysis with higher power is obtained by our recent methodology for incorporating a new marker from an external study into the PCPT risk calculator through computation of the likelihood ratio.[24] The likelihood ratio of 3-month finasteride PSA velocity will be defined as the ratio of probabilities of observing a specific 3-month finasteride PSA velocity value in cases relative to controls stratified by the PCPT risk factors. The probabilities will be modeled separately for cases and controls by linear regression with 3-month finasteride PSA velocity as outcome and covariates the PCPT risk factors: race, age, log PSA (before finasteride), DRE (before finasteride), family and prior biopsy history. By Bayes formula, an updated posterior odds of prostate cancer given 3-month finasteride PSA velocity and the PCPT risk factors is equal to the product of the likelihood ratio by the prior odds defined by the PCPT risk calculator. The posterior odds can be transformed into the posterior risk by posterior risk = posterior odds/[1+posterior odds]. (1)

Graphs of the posterior risk against the prior risk will be examined to assess the potential impact of 3-month finasteride PSA velocity as an additional risk factor to the PCPT risk factors.

*Potential pitfalls and alternative strategies for Specific Aim 4*

The standard deviations in the likelihood ratios may be high resulting in updated PCPT risks with large confidence bands (high uncertainty). These confidence bands will be displayed and reported. In this case, the need for further validation studies of 3-month finasteride PSA as a biomarker will be needed.

**6.5. Specific Aim 5:** To assess the independent predictive value of additional prostate cancer biomarkers including PCA3 and a ETS gene fusion (TMPRSS2:ERG) on the performance of the PSA-based markers and, in combination or in place of the results of the finasteride ‘challenge’ test.

*Rationale: Among a host of new biomarkers for prostate cancer, these three markers are among the most promising. This Aim will determine if they add to the performance of baseline risk assessment (using PSA and baseline demographics alone – the PCPT risk calculator), if they are superior to the finasteride ‘challenge’ results, and whether they further improve on the results of the finasteride ‘challenge’.*

**6.5.1. Study design**: At baseline, all men will undergo a DRE in which a minimum of 3 strokes are made on each lobe of the prostate after which a urine sample is obtained. After samples are obtained, one will be processed for PCA3 and the other for TMPRSS2:ERG. All samples will be de-identified at UTHSCSA prior to shipment.

**6.5.2. Sample Collection.**  Urine samples will be shipped to GenProbe for PCA3 and TMPRSS2:ERG analysis in a blinded fashion.

Specimen collection and processing for PCA3 and TMPRSS2:ERG assays: Urine samples will be collected following a DRE by applying firm pressure with several strokes to the prostate. After DRE, the first 20 to 30 mL of urine will be collected. Samples will be processed immediately using standardized methods of GenProbe; thereafter, they will be transferred to GenProbe for analysis.[23] PCA3 and PSA mRNAs in post-DRE urine are quantified using transcription-mediated amplification. PCA3 copy levels are normalized to PSA mRNA; the latter functions as a prostate-specific housekeeping gene that controls for the amount of prostate cells recovered following DRE. The final output of the assay is the PCA3 Score, defined as [(PCA3 mRNA copies/mL) / (PSA mRNA copies/mL)] x 1000. The quantitative TMPRSS2:ERG assay utilizes the same specimen type, assay format and procedure as the PCA3 assay.[37] The TMPRSS2:ERG mRNA isoform target corresponds to fusion between TMPRSS2 Exon1 and ERG Exon4.[26] TMPRSS2:ERG mRNA copy levels are normalized to PSA mRNA to yield a TMPRSS2:ERG Score.

Results of all analyses will be transmitted to [name] at UTHSCSA for analysis.

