**3.3 Procedures specific to research:**

1. Obtain signed informed consent

2. Collection of demographic information, including age, race, ethnicity, family history of prostate cancer

3. Collection of pre-biopsy urine samples to establish biomarker measurements of PCA3 and ETS gene fusion.

4. 4 to 1 Randomization to finasteride versus placebo

5. Monthly PSA lab collection

6. Pill counts

7. Collection of blood samples for prostate cancer detection, discovery,

and validation tests.

- 1. **Clinical procedures that would be done for routine care, irrespective of the research study:**

1. DRE prior to prostate biopsy
2. Prostate biopsy procedure
   1. **Subject Population**
3. **Subjects**: As this study examines prostate cancer, a disease that affects only men, only men will be enrolled. It is anticipated that the distribution of minorities in this study will reflect the minority-rich San Antonio and South Texas population. We anticipate enrolling men in the same racial/ethnic distribution as our other biomarker studies: we expect 13.5% of subjects to be African American, 37% will be Hispanic and 49.5 % Caucasian.

**Source**: Subjects will be drawn from patients seen in the Urology clinics associated with The University of Texas Health Science Center at San Antonio located at the Medical Arts Research Center (MARC), University Hospital Downtown, Robert B. Green Campus and South Texas Veterans Health Care System (STVHCS), Audie L. Murphy Division.

1. **Eligibility**

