**6.3.2. Analysis for Specific Aim 3**

Pre-finasteride PSA and DRE and 3-month finasteride PSA and DRE will be considered as four additional markers to 3-month finasteride PSA velocity measured on the same subject. Sensitivities, specificities and AUCs (excluding the dichotomous test DRE for which the AUC cannot be computed) of these markers will be determined and compared against each other and 3-month finasteride PSA velocity. Tests of differences in the AUC between all pairs of markers (excluding DRE) will be performed using the U-statistic approach of DeLong et al., which controls for the dependencies among individuals.[67] Marker sensitivities and specificities will be compared using McNemar’s test. Comparisons will be made in 2 fashions. First, the marker sensitivities will be compared at matched-specificities, e.g., cut-offs for each marker will be found which obtain 80% specificity and then sensitivities at these cutoffs will be compared. Second, and of more interest in the application, marker specificities will be compared at matched-sensitivities. We hypothesize that 3-month finasteride PSA velocity will have increased specificity (smaller false positive rate) for a given sensitivity than the other markers.

*Potential pitfalls and alternative strategies for Specific Aim 3*

The 3-month PSA and DRE endpoint will not be available from individuals who dropped out resulting in inability to make comparisons to the primary endpoint of PSA velocity and a reduction of sample size. In anticipation of incompleters, our targeted sample size of 360 subjects is inflated by 10%, for a total of 400 enrollees.

**6.4. Specific Aim 4**: To assess the independent diagnostic value of 3-month finasteride serum PSA velocity to the Prostate Cancer Prevention Trial (PCPT) prostate cancer risk calculator.

*Rationale: Extending the rationale of Specific Aim 2, we have observed that new biomarkers may not add independent prognostic value to established risk factors including family history of disease or age, in addition to standard biomarkers. Hence the ultimate goal of this study is to establish the usefulness of 3-month finasteride PSA as an independent marker to all established biomarkers and risk factors for prostate cancer.*

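### The Aim 4 test that decides whether PSA velocity is independent adjusts for four PCPT risk factors, while the next paragraph lists six; age and race are missing from the test.

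*Protocol*

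**What the plan says.** Section 6.4.1 of the protocol has two Aim 4 analyses. The first is a multivariable logistic regression for biopsy outcome, which assesses velocity "relative to the PCPT risk factors: PSA, DRE, family history and prior biopsy on this N=360 cohort". It carries a decision rule: velocity is declared to add independent information "if it retains statistical significance at the 0.05 level when included in the multivariable logistic regression along with all other risk factors".

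The second, in the next paragraph, models velocity by linear regression, separately in cases and controls, with "covariates the PCPT risk factors: race, age, log PSA (before finasteride), DRE (before finasteride), family and prior biopsy history". The resulting likelihood ratio updates the calculator's prior odds. It is assessed from graphs of posterior against prior risk, with confidence bands, and has no significance rule.

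The rationale under section 6.4 warns that "new biomarkers may not add independent prognostic value to established risk factors including family history of disease or age" and sets the goal of establishing the marker "as an independent marker to all established biomarkers and risk factors for prostate cancer". The Aim 5 rationale in section 6.5 describes baseline assessment with the calculator as "using PSA and baseline demographics alone". Section 3.3 provides for "Collection of demographic information, including age, race, ethnicity, family history of prostate cancer". Aim 5 Objective 4 (section 6.5.4) repeats the logistic rule and refers to the PCPT risk factors without listing them.

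**The concern.** One label covers two lists in adjoining paragraphs, and the shorter list belongs to the only Aim 4 analysis with a declaration rule. That model leaves out age, which the Aim's own rationale names, and race.

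A coefficient that is significant given four factors shows information beyond those four only. If the PSA response to finasteride varies with age, and age predicts the biopsy result, part of the age effect is credited to velocity. Velocity could then be declared to add to the calculator when it tells the clinician nothing that age had not already told. The same applies to race. A statistical analysis plan that follows the protocol's wording would inherit the problem.

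**Working it through.** **1. The two lists side by side (section 6.4.1)**

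| Factor | Logistic test (0.05 rule) | Likelihood-ratio model (no test) |
| --- | --- | --- |
| PSA | yes, scale not stated | yes, log, before finasteride |
| DRE | yes | yes, before finasteride |
| Family history | yes | yes |
| Prior biopsy | yes | yes |
| Age | no | yes |
| Race | no | yes |

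Four against six; the difference is age and race.

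**2. The plan's own figures.** No power is stated for the Aim 4 test. The cohort reproduces: 360 × 0.40 = 144 cases and 216 controls (section 6.2.1). The nearest stated power, 75% to 90% for the Aim 2 case-control comparison, also reproduces. With SD 0.89, the difference in log PSA change is 0.416 − 0.105 ≈ 0.310 at a 10% decline in cases, giving power 0.898. At a 15% decline it is 0.416 − 0.163 = 0.253, giving 0.750.

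**3. Size of the possible error, by formula.** Suppose velocity has no effect given age, age has odds ratio OR per SD, and age and velocity have correlation ρ. With age omitted, the velocity coefficient per SD is approximately

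b ≈ ρ × ln(OR), with SE ≈ 1/√(n·p·(1−p)) = 1/√(360 × 0.4 × 0.6) = 1/√86.4 = 0.108.

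The chance of p < 0.05 (two-sided, as sidedness is not stated) is P(Z > 1.96 − b/SE) + P(Z < −1.96 − b/SE).

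Example with OR 1.5 and ρ 0.3: b = 0.3 × 0.405 = 0.122, b/SE = 1.13, and the chance is about 0.20.

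**4. The same by simulation.** Settings: n = 360, about 40% cases, no true velocity effect, Wald test at 1.96, at least 2,000 runs per scenario (Monte Carlo error about 0.5 percentage points near 5%). Assumed log-odds: 0.4 per SD of PSA, 0.7 for DRE, 0.3 for family history, −0.4 for prior biopsy, with the three binary factors at 20% prevalence. Every age and race effect is an assumption; the protocol gives none.

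| Assumed relation | Four covariates | Six covariates |
| --- | --- | --- |
| Age OR 1.0, ρ 0.3 | about 5% | about 5% |
| Age OR 1.3, ρ 0.2 | 7% | 5% |
| Age OR 1.3, ρ 0.4 | 16% | 5% |
| Age OR 1.5, ρ 0.2 | 11% | 6% |
| Age OR 1.5, ρ 0.3 | 18% | 6% |
| Age OR 1.5, ρ 0.4 | 28% | 4% |
| Age OR 1.8, ρ 0.4 | about 50% | about 5% |
| Race OR 2, velocity shift 0.5 SD, prevalence 13.5% | 7% | 5% |
| Age OR 1.5, ρ 0.3, plus that race effect | 27% | 5% |

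With age OR 1.0 to 1.2 and ρ up to 0.2, the four-covariate rate is 4% to 8%, little different from nominal.

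**5. Room for the extra terms.** The present model has five predictors including velocity: 144/5 ≈ 29 expected cases per term. With age and one race term there are seven: 144/7 ≈ 21. With two race terms, for the three groups expected in section 3.5, there are eight: 144/8 = 18.

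**The case against.** **The decision rule can be read more widely.** It refers to all other risk factors, and the rationale names age, so six factors may have been meant. This makes the text ambiguous rather than a deliberate exclusion of age and race. The mismatch remains: the nearest antecedent is the four-item list, and if six were intended that list needs correcting.

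**Age and race are adjusted for elsewhere in Aim 4.** The likelihood-ratio model conditions on both, and the protocol presents it as the more powerful analysis. A reader might infer that Aim 4 ignores age and race altogether; it does not. But that model has no test and cannot overturn a declaration made by the logistic regression.

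**The protocol already concedes limits.** It warns of limited power for the logistic analysis and says that the study is designed mainly for Aims 2 and 3 and the first three objectives of Aim 5. That lowers the weight of the point. Limited power, however, concerns missed effects; an omitted confounder can produce false ones.

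**The calculator's equation is not in the protocol.** A reader might infer that the four-item list is proved to misstate the calculator. The documents do not settle which terms its equation uses. What they show is two lists under one label, and a stated goal that the shorter list does not meet.

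**PSA scale.** A reader might also infer that PSA enters untransformed in the logistic model. The text gives no scale there, and functional form can properly be left to the analysis plan.

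**Conclusion.** The point holds as an inconsistency with a specific consequence. The four-factor logistic model does not test independence from all established risk factors, because it leaves out age, which the rationale names, and race, which the protocol itself counts among the PCPT risk factors one paragraph later. The mismatch is certain from the text.

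The size of the consequence is not. It needs age or race to be related to both velocity and biopsy outcome, and the protocol gives no figure for either relation. Across the assumed age effects (OR 1.0 to 1.8 per SD, correlation 0 to 0.4) the false-declaration rate runs from about 5% to about 50%. The upper end is an extreme corner of the assumptions and should not be read as the expected error rate; with weak confounding there is practically no inflation. Race alone, under the one strong scenario shown, gives only 7%. With both covariates included the rate stays near 5% throughout.

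The text should be corrected, but the point does not touch the primary endpoint.

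**What to change.** Define the PCPT risk factors once, as race, age, log baseline PSA, DRE, family history and prior biopsy, with PSA and DRE taken before finasteride. Use that set in both Aim 4 models and in the logistic model of Aim 5 Objective 4, and let the 0.05 rule refer to it explicitly.

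The change is one of wording; age and race are already collected. Its statistical cost is two extra parameters, or three if race takes two terms, which leaves about 18 to 21 expected cases per term. Some apparent significance may be lost where velocity is correlated with age, but part of that was age information and not evidence for velocity.

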**3. Research Design and Methods**

**3.1 Primary Objective:** To determine if a five alpha reductase ‘challenge’ with finasteride improves the performance of the combination of PSA and DRE in men who are scheduled for prostate biopsy.

**3.2 Secondary Objective:** To evaluate the independent predictive value of other prostate cancer markers including PCA3, TMPRSS2:ERG,and 3-month finasteride PSA velocity on the performance of the PCPT risk calculator.

**Procedures:** After informed consent, eligible subjects will be randomized in a 4:1 manner (for the rationale of choosing a 4:1 randomization schema see power calculation under Specific Aim 2) to receive a bottle containing 100 tablets of finasteride 5mg or placebo and will take one tablet daily for three months. PSA will be measured monthly. Serum PSA samples will be sent to Quest Diagnostics for analysis. At baseline and at 3-months (90 days + 7 days), subjects will undergo PSA, DRE, PCA3, and TMPRSS2:ERG fusion. Post-DRE urine samples will be sent for analysis.

Specimen collection and processing for PCA3 and TMPRSS2:ERG assays: Urine samples will be collected following a routine DRE After DRE, the first 20 to 30 mL of urine are collected. Samples will be processed immediately using standardized methods of GenProbe; thereafter, they will be transferred for analysis.[21] PCA3 and PSA mRNAs in post-DRE urine are quantified using transcription-mediated amplification. PCA3 copy levels are normalized to PSA mRNA; the latter functions as a prostate-specific housekeeping gene that controls for the amount of prostate cells recovered following DRE. The final output of the assay is the PCA3 Score, defined as [(PCA3 mRNA copies/mL) / (PSA mRNA copies/mL)] x 1000. The quantitative TMPRSS2:ERG assay utilizes the same specimen type, assay format and procedure as the PCA3 assay.[22] The TMPRSS2:ERG mRNA isoform target corresponds to fusion between TMPRSS2 Exon1 and ERG Exon4.[23] TMPRSS2:ERG mRNA copy levels are normalized to PSA mRNA to yield a TMPRSS2:ERG Score.

Specimen collection for research: Approximately two tablespoons of blood in approximately two tubes will be drawn from a vein in the participant’s arm. This blood will be used for the development of prostate cancer detection, discovery, and validation tests. One tube will be for serum and DNA and the other for plasma and dimethyl sulfoxide (DMSO) preserved white blood cells.

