**Inclusion Criteria:**

1. Risk of prostate cancer 20-60% calculated with the on-line PCPT prostate cancer risk calculator. (www.prostate-cancer-risk-calculator.com).[15] PSA value must be obtained within 3 months prior to study entry. A description of the frequency of these individuals in the population is provided in Specific Aim 2.

1. Patient has been recommended to undergo and plans to have a prostate biopsy.
2. Patient is willing to delay prostate biopsy for a 3-month finasteride treatment.
3. No allergy to finasteride or other five alpha reductase inhibitors.
4. Patient is willing to take finasteride 5 mg orally daily for 3-month treatment period.
5. Age 55 or older. (This age is selected as the PCPT risk calculator is only valid for this age range.)

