**6. Data Analysis**

**6.1 Statistical Considerations for the Study**

Statistical endpoints of the study and definitions of terms are first provided for reference for the statistical plan for Specific Aims 2-5. Lists of analysis plans and power calculations follow for the required sample size of 500 (144 expected cancer cases in finasteride arm; 216 expected controls in finasteride arm; 90 subjects in placebo arm; 10% inflation for drop-out).

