**6.2.1. Power estimates for Specific Aim 2**

Sample size is selected to ensure sufficient accuracy for characterizing the operating characteristics (sensitivity and specificity) of 3-month finasteride PSA velocity and to have adequate power to detect the difference in PSA decline between cases and controls (non-cases). We estimate a positive biopsy rate of 40% in study subjects. Thus, the ratio of cancer cases to non-cases (controls) is 0.67(=0.4/0.6). With finasteride, a decline of 34% was seen in controls by 3 months[6]; a decline of 10-15% in cancer cases is assumed, corresponding to an additive change on a logarithmic PSA scale (in order to assume normality) of -log(1-0.34)=0.416 for controls, and -log(1-0.10)=0.105 to –log(1-0.15)=0.163 for cases. An estimate of the standard deviation of log PSA from the 3379 SABOR cohort is .89. Assuming a correlation of .5 between two PSA measures from the same patient (before and after finasteride) implies the same standard deviation for the difference or change in log PSA over 3-months. With these assumptions, a sample of 360 (144 cancer cases and 216 controls) in finasteride arm achieves a 75% to 90% power to test the null hypothesis that there is no difference between cases and controls in 3-month finasteride PSA change with a significance level (alpha) of 0.05 using a two-sided two-sample t-test (Table IX).

Table IX: Power for 216 Controls (no PCa) and 144 Cases (PCa) in Finasteride Arm

| PSA decline in | PSA decline in cancer cases | | | | |
| --- | --- | --- | --- | --- | --- |
| Controls | 8 % | 10% | 12% | 14% | 16% |
| 30 % | **.814** | **.747** | .665 | .574 | .479 |
| 32 % | **.884** | **.833** | **.766** | .687 | .598 |
| 34 % | **.934** | **.900** | **.851** | **.788** | .713 |
| 36 % | **.966** | **.944** | **.912** | **.867** | **.809** |
| 38 % | **.984** | **.973** | **.954** | **.926** | **.886** |
| 40 % | **.994** | **.988** | **.979** | **.963** | **.939** |

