**6.5.4. Analysis for key objectives**

- Objectives 1 to 3

Tests of differences in the AUC between all pairs of markers (Objective 1: PCPT RC vs. PCA3 and PCPT RC vs. TMPRSS2:ERG; Objective 2: PSA velocity vs. PCA3, PSA velocity vs. TMPRSS2:ERG; Objective 3: posterior risk vs. PCA3, posterior risk vs. TMPRSS2:ERG) will be performed using the U-statistic approach of DeLong et al.[67] Marker sensitivities will be compared at matched-specificities; marker specificities will be compared at matched-sensitivities. The same power calculation as for Specific Aim 3 applies.

- Objective 4

Multivariable logistic regression will be used to ascertain whether 3-month finasteride PSA velocity, PCA3 and TMPRSS2:ERG add independent diagnostic information for predicting cancer outcome on biopsy relative to the PCPT risk factors in this cohort. A new biomarker will be declared to add independent diagnostic information if it retains statistical significance at the .05 level when included in the multivariable logistic regression along with all other risk factors. This analysis may have limited power since the cohort is relatively small and several risk factors will be estimated.

In addition, the approach of Ankerst et al. (2008)[24] will be used to combine the predictive information of the new biomarkers. In Specific Aim 4, we plan to upgrade the PCPT risk calculator by including the 3-month finasteride PSA velocity. In Specific Aim 5, four types of updates of the PCPT risk calculator will be examined: 1) adding a single marker (PCA3, TMPRSS2:ERG, , or PSA velocity); 2) adding two markers at a time (6 possibilities); 3) adding three markers at a time (4 possibilities); and 4) adding all four biomarkers. In each case, likelihood ratios for the biomarkers will be modeled using normal distribution (for Type 1 update) or multi-normal distribution (for Type 2-4 updates) for inclusion of new biomarkers with means conditional on PCPT risk factors. The likelihood ratios will be multiplied by the prior odds of prostate cancer of the PCPT risk calculator to form the posterior risks of prostate cancer. Risk curves and surfaces will be examined to assess the potential impact of new biomarkers as additional risk factors to the PCPT risk factors for Type 1 update and Type 2-4 updates, respectively.

*Potential pitfalls and alternative strategies for Specific Aim 5*

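### The likelihood-ratio update of the PCPT calculator is read only from graphs of risk movement, so the plan never tests whether the updated risks predict biopsy better than the original ones

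*Protocol*

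**What the plan says.** Protocol section 3.2 sets as secondary objective the predictive value of PCA3, TMPRSS2:ERG and PSA velocity "on the performance of the PCPT risk calculator". Section 6.4.1 (Aim 4) gives two analyses.

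- **Logistic regression.** Velocity is declared to add independent information if it is significant at 0.05 alongside the PCPT risk factors. The protocol concedes limited power.
- **Likelihood-ratio update.** This is introduced with "An analysis with higher power is obtained by our recent methodology". Velocity is regressed on race, age, log PSA, DRE, family history and prior biopsy, separately in cases and in controls. The ratio of the two fitted densities multiplies the calculator's prior odds. The stated reading is: "Graphs of the posterior risk against the prior risk will be examined to assess the potential impact of 3-month finasteride PSA velocity".

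If uncertainty is large, confidence bands will be shown and further validation is said to be needed.

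Section 6.5.4 (Aim 5, Objective 4) says "we plan to upgrade the PCPT risk calculator by including the 3-month finasteride PSA velocity" and extends the update to sets of markers, with the same kind of reading: "Risk curves and surfaces will be examined to assess the potential impact of new biomarkers". The AUC comparisons listed there for Objectives 1 to 3 set posterior risk against PCA3 and against TMPRSS2:ERG. They do not set it against the PCPT calculator.

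**The concern.** A graph of posterior against prior risk contains no biopsy outcome. It displays reclassification, and reclassification happens whether the marker is informative or the fitted ratio is noise. Two regressions with six or more covariates, fitted in groups of this size, will differ by chance, so the fitted ratio departs from 1 for a marker of no value. The plan therefore has no criterion that answers its own question about performance in the analysis it presents as the more powerful one. What is at stake is an updated calculator that looks useful in the trial's data but predicts no better, or worse, in new men.

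**Working it through.** **Inputs from the protocol.** Section 6.1: "144 expected cancer cases in finasteride arm; 216 expected controls in finasteride arm". Section 6.2.1: "We estimate a positive biopsy rate of 40% in study subjects"; log-scale declines of 0.416 in controls and 0.105 to 0.163 in cases; SD 0.89. Inclusion Criteria: "Risk of prostate cancer 20-60% calculated with the on-line PCPT prostate cancer risk calculator".

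**The plan's own figure.** The update has no stated figure, but the inputs reproduce the power in section 6.2.1. The standard error is 0.89 × √(1/144 + 1/216) = 0.0958. For 10% against 34%, 0.310/0.0958 = 3.24, giving power 0.898. For 15% against 34%, 0.253/0.0958 = 2.64, giving power 0.750. These match the stated 75% to 90%.

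**Why risks move for a worthless marker.** Scale velocity to residual SD 1 and let e be a man's true residual. To first order, the fitted log ratio under no association is

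e × (error in case mean − error in control mean) + ½(e² − 1) × (error in case variance − error in control variance).

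With k coefficients per regression its variance is about k(1/n₁ + 1/n₀) + ½[2/(n₁ − k) + 2/(n₀ − k)].

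- k = 7 (intercept and six covariates): 7 × 0.01157 = 0.0810; 1/137 + 1/209 = 0.0121; sum 0.0931; SD 0.305.
- k = 8 (race at three levels): 0.0926 + 0.0122 = 0.1048; SD 0.324.
- k = 1 (no covariates): 0.0116 + 0.0116 = 0.0232; SD 0.152.

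This needs no assumed covariate distribution. It shows that most of the spread comes from the covariate regressions. For a man at 40% prior risk, a one-SD shift of 0.31 turns odds of 0.667 into 0.667 × 1.363 = 0.909, a risk of 47.6%, or about 8 points.

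**Simulated trials of 360 men, worthless marker.** The documents do not give covariate distributions, so these are assumed: prior risk 20-60%, calibrated prior, prior AUC about 0.62, normal residuals. Across several assumed covariate sets:

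| Quantity | Result |
|---|---|
| SD of log likelihood ratio | 0.31 to 0.33 |
| Men moved by 5 points or more | 28% to 31% |
| Men moved by 10 points or more | 10% to 13% |
| AUC change, trial's own data | +0.024 to +0.03 |
| AUC change, new men | about −0.02; negative in over 99% of trials |
| Brier score change, new men | about +0.005 (worse) |

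**At the protocol's own effects.** For 15% against 34%, AUC appears to rise by 0.04 to 0.05 in the trial's data, but the gain in new men is only 0.00 to 0.01. The Brier score in new men is worse than the unmodified calculator's in about 60% of trials in two sets of runs and 47% in a third. For 10% against 34% the update does help on average: AUC in new men rises by about 0.02, and log loss is worse in only about 20-25% of trials. Risk movement is larger than for a worthless marker in both cases, but the ranges overlap, so a graph cannot separate the situations.

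**The case against.** **The formal claim is protected.** Independent information is declared only through the logistic test at 0.05, which was significant in 5.1% of simulated null trials. The graphs are said to assess potential impact, and section 6.4.1 and the Aim 5 pitfalls text foresee wide bands, further validation or a larger study. Aim 4 and Objective 4 lie outside the stated power focus. All of this stands, and it lowers the stakes. However, the logistic test does not evaluate the updated risks, and section 6.5.4 does not make the update depend on it.

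**The bands would reveal noise.** Under no association, pointwise 95% bands excluded a ratio of 1 for about 4% of men on average. They behave as they should, but they measure precision, not performance, and no rule for reading them is given.

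**Both AUCs will be computed anyway.** Objectives 1 and 3 use the calculator and the posterior risk on the biopsy outcome. The direct contrast between them is still not planned, and the posterior's AUC would be in-sample.

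**Validation detail belongs in a SAP.** The resampling scheme may. But the protocol itself fixes the reading, and that reading does not address the objective.

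Two stronger readings are not supported. A reader might infer that most null trials would be reported as showing impact. The share depends on a cut-off the protocol does not set: it ran from 4% (at least one man in five moved more than 10 points) to 88% (95th percentile of movement above 10 points). A reader might also infer that the likelihood-ratio analysis has lower power than the logistic test. That needs a joint test of all differing coefficients, which nobody plans. What can be said is that no test is attached, so the higher-power statement has no support in this document.

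**Conclusion.** The concern holds as a mismatch between objective and criterion. The planned reading of the likelihood-ratio update cannot show whether the calculator's performance improves, and the missing comparison is posterior against PCPT risk on the biopsy outcome. Estimation error alone gives a log-ratio SD of about 0.3. In the simulations an apparent in-sample AUC gain of about 0.025 goes with a loss of about 0.02 in new men. The SD follows from the group sizes and the number of coefficients. The other figures depend on assumed covariates, a calibrated prior and normal residuals; their direction under no association did not change across the covariate sets tried. The Brier result at 15% against 34% is the least stable figure and should be read as roughly half to three fifths of trials. Nothing here shows that a worthless marker would be formally declared useful, or that a calculator would be released on the graphs alone.

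**What to change.** In sections 6.4.1 and 6.5.4:

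1. Add a comparison of posterior with prior (PCPT) risk on the biopsy outcome, using cross-validated or bootstrap optimism-corrected AUC, Brier score and calibration, each with a confidence interval.
2. Label the posterior-against-prior graphs and the risk curves and surfaces as descriptive.
3. Add a logistic model with the PCPT log-odds as offset and one coefficient per marker. This uses the calculator's prior information without re-estimating its factors.
4. Delete the higher-power statement, or qualify it by naming the test it refers to.

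Do not make the upgrade conditional on a 95% confidence interval for the AUC gain excluding zero. In a simulation of the offset model with 10-fold cross-validation, that condition was met in only about 13% of trials at 10% against 34% and 5% at 15% against 34%, while the offset test itself had 88% and 71% power.

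The cost is some analysis work and no new data. The reported gain will look smaller than the in-sample one.
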